### Outcomes

#### Primary outcome

Total number of sickness absence days during the 6 months after enrolment in the study (i.e. after pre-screening), obtained by national registers.

#### Secondary outcomes and additional measures

Secondary outcomes include additional sickness absence measurements, health related quality of life, health related behavior, functional status, somatic- and mental health, and perceptions of work and returning to work. Particularly we will measure:

• Time until full sustainable RTW (i.e. for at least 4 weeks without relapse).

• The proportion of workers at work will be obtained by national registers and a self-report of social security benefits received from NAV (The Social Security Office).

• One, three and five-year follow-up of total registered days of physician referred sick leave by national registers.

• Readiness, beliefs and motivation for Return to Work, measured by Readiness for Return to Work Scale
[28] and the questions: “How long do you think you will be on sick leave from today” (Not at all, less than 1 month, 1–2 months, 2–4 months, 4–10 months, more than 10 months), “Do you want to return to work” (yes/no), “How strongly do you want to return to work” (not at all-very much, 1, 2…-10).

• Health-related quality of life by 15D (15 dimensions)
[29].

• Perceived general health with the question: How is your health now?

• Pain intensity and pain sites by a body pain chart; and question 3–5 from the Brief Pain Inventory
[30].

• Catastrophizing thoughts regarding pain by two questions from the Coping Strategies Questionnaire
[31].

• Symptoms of depression and anxiety by the Hospital Anxiety and Depression Scale
[32].

• Subjective health complaints by the SHC Inventory
[33].

• Physical activity levels measured by the International Physical Activity Questionnaire
[34], and three additional items concerning frequency, intensity and duration of exercise from the third wave of the HUNT study
[35].

• Physical, social and emotional functional status measured by the first four charts of COOP/WONKA
[36].

• Four subscales (Job Demands, Control at work, Mastery of work and Social interactions at work) from The general Nordic questionnaire for psychological and social factors at work (QPSnordic)
[37].

• Duration and intensity of complaints and interruption with work tasks. The original questions referred to pain only
[38], but we modified them so they would apply to all complaints.

• Fear of movement in relation to work and physical activity, with the Fear Avoidance Beliefs Questionnaire
[39].

• Psychological flexibility and acceptance by the Acceptance and Action Questionnaire-II
[40].

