### Study population

Persons living in the counties of Trøndelag, population of 375 000 inhabitants, are eligible for inclusion if they are 18–60 years old and have been on sick leave 2–12 months, with a current sick leave status of 50% - 100%. Individuals with an ICPC-2 (International Classification of Primary Care, Second edition) diagnosis within the L (musculoskeletal), P (psychiatric) or A (unspecific disorders) categories are eligible. Thus both persons being on sick leave due to musculoskeletal and psychological disorders, chronic pain, fatigue and other non-specific disorders are included in the study. Exclusion criteria are: 1) alcohol or drug abuse; 2) serious somatic (e.g. cancer, heart disease) or psychological disorder (e.g. suicide attempts, psychosis, ongoing manic episode); 3) a specific disorder requiring specialized treatment; 4) pregnancy; 5) currently participating in another treatment program; 6) insufficient comprehension of Norwegian language to participate in group sessions and to fill out questionnaires; 7) scheduled for surgery within the next 6 months; and 8) serious problems with functioning in a group setting.

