### Data collection

Data on sickness benefits and other social benefits will be based on register data from Statistics Norway as long as 5 years after participation in one of the rehabilitation programs. Self-reported data will be collected by electronic questionnaires via the internet (http://www.checkware.com) before pre-screening, at pre-test, post-test, and 3, 6 and 12 months after pre-test. Qualitative data will be collected through semi-structured focus group interviews, through individual interviews, and participant observations. Interviews will be based on an interview guide, audio recorded and transcribed. Some participants will keep notebooks during and after the rehabilitation program to explore their experience of the RTW process.

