## Discussion

Sick leave is a major problem in the western world. Norway is considered to have a high level of sick leave
[43], and approximately 10% of the workforce is on disability pension
[44]. Hence, it is necessary to develop services that help people to stay at work, including effective rehabilitation models.

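### The 1-, 3- and 5-year outcomes count only certified sick-leave days, so a move to disability pension is scored like a return to work

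*Protocol article*

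**What the plan says.** Under Secondary outcomes and additional measures, the long-term outcome is "One, three and five-year follow-up of total registered days of physician referred sick leave by national registers". No other benefit is named in that item.

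Under Primary outcome, the 6-month measure is "Total number of sickness absence days during the 6 months after enrolment in the study (i.e. after pre-screening), obtained by national registers". The term is not defined further.

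Under Data collection, the register extract is wider than either outcome: "Data on sickness benefits and other social benefits will be based on register data from Statistics Norway as long as 5 years" after participation.

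Two other secondary outcomes bear on the point. One is "Time until full sustainable RTW (i.e. for at least 4 weeks without relapse"; the other is work status: "The proportion of workers at work will be obtained by national registers and a self-report of social security benefits received from NAV".

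Under Study population, people enter at a sick-leave degree of 50% to 100%. Under Health economics, sickness absence days are the effect measure of the cost-effectiveness analysis. The Discussion notes, as background, that "approximately 10% of the workforce is on disability pension".

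**The concern.** A count of days on one benefit measures absence from work only while absent people stay on that benefit. Over one to five years, some people with long sick leave can be expected to move to disability pension or another health-related benefit. Under the long-term definition as written, their count stops on the day of transfer, just as it does for someone who resumes full work. The least favourable work outcome is then scored like the most favourable one.

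For the comparison of arms, the effect depends on the transfer rates. If one arm has more transfers, its mean day count falls for a reason unrelated to recovery. A programme that prevented disability pension by keeping people on sick leave for longer, on the way back to work, could look worse than its comparator. If the rates are equal, the arms are not systematically separated, but the outcome no longer describes time away from work. The Background names permanent work disability among the things such programmes exist to prevent, so the outcome is weakest where the trial's purpose is strongest.

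**Working it through.** **1. The plan's own figure.** Sample size assumes means of 60 (SD 40) and 90 (SD 60), P = 0.05 and 90% power. The pooled SD is √((40² + 60²)/2) = 50.99. Then n = 2 × (1.960 + 1.282)² × 50.99² / 30² = 60.7, so 61 per group, as stated. The point does not rest on an arithmetic error; the planned 30-day difference serves below only as a yardstick.

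**2. Ranking of individual courses over 365 days** (constructed examples):

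| Course | Certified sick-leave days | Days on any health-related benefit |
|---|---|---|
| 60 days sick leave, then another health benefit | 60 | 365 |
| 120 days sick leave, then full return to work | 120 | 120 |

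The count as written ranks the first course as better. Counting all health-related benefits reverses the order.

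**3. Shift in the 1-year mean.** The article gives no transfer rates or dates. Assumptions: transfer at day 182; an excess share e of transfers in one arm.

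Maximum shift = e × (365 − 182) = e × 183 days.

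- e = 5 points: 9.2 days
- e = 10 points: 18.3 days
- e = 20 points: 36.6 days

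**4. Why this is a ceiling.** The days removed are those the person would otherwise have spent on certified sick leave after the transfer date, anywhere from 0 to 183. If the average were half of 183, the shifts would halve to about 4.6, 9.2 and 18.3 days. As a further assumption not stated in the article, suppose a sick-leave spell ends at 12 months. The earliest entrant, at 2 months, then has 10 months left. Transfer at month 6 removes at most 4 months from that spell, 4 × 365/12 = 122 days, so 5 to 20 points give at most 6 to 24 days.

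**5. Three and five years.** The same formula over 1,095 and 1,826 days gives 91 and 164 days for a 10-point excess. Those values require that the person would otherwise have stayed on certified sick leave without a break for years. They are not used as estimates.

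**6. The 6-month primary, if it too counts only sick leave.** With transfer at day 91, the maximum shift is e × (182 − 91) = e × 91: 4.6, 9.1 and 18.2 days for 5, 10 and 20 points. An excess of 30/91 = 33 points would be needed to produce the whole planned difference. If the excess lies in the comparator, a true 30-day benefit shrinks to at least 25.5, 20.9 or 11.8 days. These are shifts in means. The primary test is Mann-Whitney, so they do not translate directly into its result.

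**7. Graded leave.** A full year at 50% counts as 365 days if calendar days are counted, and as 365 × 0.5 = 182.5 if weighted by degree. The article does not say which rule applies.

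**The case against.** The strongest reply is that this is a condensed article. Which register codes count, how degrees are weighted and how transfers are handled in the survival analysis are commonly left to an analysis plan, which is not shown. For the primary outcome and the weighting of graded leave, that reply stands: the article is silent there, and silence is not an error.

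Two stronger readings are therefore tempting but unsupported. A reader might infer that the primary also scores a transfer as zero, since the Abstract, Sample size and Statistical analyses sections speak of sick leave days. The outcome definition itself says sickness absence and names no benefit, so this is possible but not stated. A reader might also infer that a part-time return is scored like full absence. No section says so, and such a rule would hide a good result rather than reward a bad one.

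The reply does not reach the long-term outcomes. There the article itself fixes the narrow count, alongside a data collection that includes the other benefits.

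A second reply is that work status and time to sustainable return to work would expose transfers. They would do so in part. Both are separate outcomes that leave the day counts unchanged, and the relapse condition does not say whether a move to pension counts as non-return.

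A third reply is that nothing in the article shows differing transfer rates. That is correct. The 10% in the Discussion describes the workforce, not transitions in this trial.

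**Conclusion.** The point holds for the 1-, 3- and 5-year outcomes. Applied as written, they give no further days after a move to disability pension or another health-related benefit, and they can rank a worse course above a better one. Bias between arms requires transfer rates that differ; with equal rates, the loss is one of meaning.

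The size is unknown. On assumed excesses of 5 to 20 points and transfer at 6 months, the 1-year mean moves by at most about 9 to 37 days, and by less to the extent that those people would have left sick leave anyway. A reader might extrapolate to hundreds of days per arm at 5 years, but the documents give no basis for assuming sick leave of that length.

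The 6-month primary and the cost-effectiveness days are undefined as to benefit and degree. They may share the problem, to a smaller extent at 6 months, but the text does not establish that they do.

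**What to change.** - Define the 1-, 3- and 5-year counts as days on any health-related benefit (sick leave, other temporary health-related benefit, disability pension) from the register, weighted by registered degree where available.
- Apply the same definition to the 6-month primary and to the days used in the cost-effectiveness analysis.
- State that a move to disability pension does not count as sustainable return to work.
- Keep certified sick-leave days as a sensitivity analysis, so that the count now described is still reported.

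The cost is wording and some extra register programming. The other social benefits are already in the planned data collection; benefit degree must also be in the extract for the weighting to be possible. The definitions should be fixed before outcome data are compared by arm.

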#### Health economics

Cost-effectiveness and cost-utility will be evaluated from a societal perspective where both direct and indirect costs will be measured according to Norwegian guidelines for economic evaluation
[41]. Direct costs comprise health services used, while indirect costs are loss of productivity due to sick leave. Treatment costs will be estimated specifically for the two interventions and for the comparative intervention based on standardized individual patient programs and a micro-costing approach. In the cost-effectiveness analysis, sickness absence days will be used as outcome measure, and to avoid double counting productivity costs will be excluded. In the cost-utility analysis, the outcome measure is Quality Adjusted Life Years based on the 15D instrument (22), and productivity costs will be included. In both cost-effectiveness and cost-utility analysis, the incremental ratio will be calculated by dividing the incremental cost by the incremental effect. Bootstrapping procedures will be used to estimate uncertainty surrounding the cost-differences and the incremental ratio. Sensitivity analysis will be applied and cost-effectiveness plane and acceptability curves used for additional presentation purposes.

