**Figure 1 F1:**
[figure not shown]
**Design of the study.** ACT: Comparative outpatient Acceptance and Commitment Therapy Rehabilitation group.

• Are the multicomponent rehabilitation programs more effective in reducing sickness absence compared to the single component Acceptance and Commitment Therapy (ACT) program (i.e. Short vs. ACT; Long vs. ACT), and are there differences between the Long and Short programs?

• Are the multicomponent rehabilitation programs cost effective compared to the single component ACT program (i.e. Short vs. ACT; Long vs. ACT)?

• Are the patients’ and service providers’ expectations before participation in the multicomponent rehabilitation programs, in accordance with their experiences afterwards?

• According to the patients’ and service providers’ experiences; have the multicomponent rehabilitation program been implemented as planned?

• Are the multicomponent programs more effective in improving secondary outcomes (e.g. mental or physical health, or motivation for return to work) than the single component Acceptance and Commitment Therapy (ACT) program?

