### Sample size

Three approaches have been performed to determine sample size:

1) Comparison of number of days with sick leave at 6 months of follow-up (P = 0.05; 90% power): An average of 60 days (SD 40) and 90 days (SD 60) of sick leave in the intervention and comparative group, respectively would require 61 persons for each group.

2) Comparison of time to sustainable RTW with Kaplan Meier survival analysis with log rank test with a hazard ratio of 0.6 (alpha 0.05, beta 0.20) would require 63 in each group (secondary outcome).Comparison of the share of workers after one year with the same statistical assumptions as point 1; 60% versus 40% RTW would require 68 people in each group. (secondary outcome).

Accordingly, with estimated ~20% loss to follow-up we will include 80 persons in each arm.

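### The economic analysis bootstraps the incremental cost-effectiveness ratio and treats the plane and acceptability curves as extras, so its uncertainty measure becomes unreadable when the effect is near zero

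*Protocol article*

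**What the plan says.** The Health economics section of the protocol article plans a cost-effectiveness analysis on days of sick leave and a cost-utility analysis on quality-adjusted life years from the 15D. One rule serves both: "In both cost-effectiveness and cost-utility analysis, the incremental ratio will be calculated by dividing the incremental cost by the incremental effect". For the first of these, "In the cost-effectiveness analysis, sickness absence days will be used as outcome measure, and to avoid double counting productivity costs will be excluded".

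On uncertainty it states: "Bootstrapping procedures will be used to estimate uncertainty surrounding the cost-differences and the incremental ratio". Sensitivity analysis is also planned, with "cost-effectiveness plane and acceptability curves used for additional presentation purposes".

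The section gives no costs, no willingness-to-pay range and no named type of bootstrap interval. The principal research questions, listed with Figure 1, ask whether each inpatient programme is cost effective compared with ACT. They also ask whether it is "more effective in reducing sickness absence compared to the single component Acceptance and Commitment Therapy (ACT) program", so fewer days is the benefit.

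**The concern.** A ratio keeps only the quotient of two differences and loses the sign of each. Two opposite situations give a negative cost per day averted: the programme costs less and works better (dominant), or costs more and works worse (dominated). Coding the effect as days rather than days averted makes both positive, so they still share a sign. The ratio also jumps from very large positive to very large negative as the effect passes through zero.

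If nearly all bootstrap replicates of the effect lie on one side of zero, this does no harm. If they straddle zero, an interval for the ratio mixes replicates that mean opposite things. Its negative part can be read as cost saving when it comes from replicates in which the programme is dominated. Cost-effectiveness is a stated principal question, so its main measure of uncertainty should stay readable when the benefit is modest.

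**Working it through.** **Inputs from the protocol article, Sample size section.** "An average of 60 days (SD 40) and 90 days (SD 60) of sick leave" in the intervention and comparative group respectively; two-sided 5% taken for the stated P = 0.05; 90% power; 80 per arm with about 20% loss, so 80 × 0.8 = 64.

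**Assumed.** The documents give no cost, so each programme is taken to cost a fixed amount C more per person than ACT. The effect is days averted (ACT mean minus programme mean), with normally distributed replicates.

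**The plan's own figure.** The average SD is √((40² + 60²)/2) = 50.99. With a difference of 90 − 60 = 30 days, 5% two-sided and 90% power, the required size is 61 per group, as stated.

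**Standard error of the difference in days.** √((40² + 60²)/n) = √(5200/n), which is 9.01 days at n = 64 and 8.06 at n = 80.

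**Sign check, with illustrative costs.**
- Dominated: cost +30,000 and 5 more days gives 30,000/(−5) = −6,000 per day averted.
- Dominant: cost −5,000 and 30 fewer days gives −5,000/30 = −167 per day averted.

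Both are negative, and the worse result is the lower number.

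**Ratio interval for a given observed benefit, 64 per arm.** The share of replicates on the harmful side is Φ(−benefit/SE). The interval is the central 95% of C divided by days averted.

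| Observed benefit | Replicates harmful | 95% interval, per day averted |
|---|---|---|
| 30 days | 0.04% | 0.021C to 0.081C |
| 15 days | 4.8% | −0.34C to +0.53C |
| 10 days | 13% | −0.89C to +1.02C |

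In the last two rows the lower limit is negative although every replicate costs C more. That no replicate saves money follows from fixing the cost. The negative limit comes only from the harmful replicates.

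**How often a trial would meet this.** The interval mixes signs in this way when more than 2.5% of replicates are harmful, that is, when the observed benefit is below 1.96 × SE. The probability is Φ(1.96 − true benefit/SE). For 30 days and 80 per arm: 30/8.06 = 3.72, and Φ(1.96 − 3.72) = Φ(−1.76) = 0.039.

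| True benefit | 80 per arm | 64 per arm |
|---|---|---|
| 30 days | 4% | 9% |
| 20 days | 30% | 40% |
| 15 days | 54% | 62% |
| 10 days | 76% | 80% |

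In other words, the ratio interval fails in those trials where the mean difference in days is not significantly favourable.

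**Comparison with net benefit.** Assume an extra cost of 30,000, a cost SD of 40,000, a threshold of 3,000 per day averted, 80 per arm and an effect of 5 days. Then 54% of replicates have a ratio below the threshold, but only 27% have positive net benefit. The gap of 27 percentage points is the share of dominated replicates, which a simple reading of the ratio counts as favourable.

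**The case against.** The strongest reply is that the plan already contains the remedy. A plane shows replicates by quadrant, and acceptability curves cover a range of willingness to pay, so a reader of the full report could tell dominated from cost-saving results. No percentile interval or ranking of ratios is named. At the planned 30-day effect the ratio interval is usable; benefits of 15 or 10 days appear nowhere in the protocol article, and every cost input is assumed. Sick leave comes from national registers, which the Strengths section says cover non-responders, so 80 per arm may suit this outcome better than 64.

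Most of this stands, and it reduces the size of the point. It does not remove it. The article goes beyond leaving details to a fuller plan: it names the ratio as a bootstrap target and gives the plane and curves the lesser role. The difficulty does not depend on the percentile method, because the ratio is discontinuous at zero effect. A benefit below 30 days is also plausible, since Table 1 shows ACT-based group sessions in all three programmes.

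A stronger reading is tempting: that dividing by sickness absence days, where fewer is better, gives an effective programme a negative ratio (60 − 90 = −30 days), so that the plan reverses the sign. The documents do not support this. Nothing defines the increment as programme days minus ACT days, and the research questions frame effectiveness as a reduction, so days averted is the natural reading. Even on raw days the ratio is negative for an effective programme only if it also costs more.

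**Conclusion.** The point holds in a limited form. The ratio is a poor quantity on which to base the uncertainty statement, because its interval stops being interpretable when effect replicates straddle zero. The consequence is negligible to small if the planned 30-day benefit is real (4% to 9% of trials). It is common if the benefit is half that or less (54% to 80% at 15 and 10 days).

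These shares rest on the plan's SDs, normal replicates and an assumed fixed extra cost. The intervals also assume a percentile-type summary. The same weakness applies in principle to the cost-utility ratio when the difference in quality-adjusted life years is near zero. It cannot be sized, as no variability is given for the 15D.

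The randomised comparison of sick leave is untouched. This is an inexpensive improvement to a secondary analysis that answers a principal question, and no error of sign has been shown.

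**What to change.** In the health-economics plan:

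- Bootstrap the pair (incremental cost, incremental effect) for each comparison with ACT.
- Make the planned plane and acceptability curves, with a bootstrap interval for incremental net benefit over a stated range of willingness to pay, the main uncertainty result.
- Report the ratio as a point estimate with its quadrant named, and give no interval for it when effect replicates fall on both sides of zero.
- As a clarification, word the cost-effectiveness outcome as sickness absence days averted, so that positive means benefit in both analyses.

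The same replicates serve and no new data are needed. The one drawback is that net benefit must be shown over a range of thresholds instead of as a single figure with an interval.
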